### Randomization

Randomization in blocks of 80 was conducted by the study pharmacist (who was blinded to enrollment and outcome measurement) using the ‘first generator’ on the website: www.randomization.com in September 2013. These numbers then become the new identification numbers on the treatment packs. All treatment packs are then distributed to participating clinics by the study pharmacist who sends out five sequentially numbered treatment packs to each participating site as sites are recruited to the study. The study pharmacist is the only person with access to the master code to the randomized treatments. The participants, recruiting clinicians and investigators will be blinded to the controlled and randomized 10-day treatment pack that is given to the study participant. Blinded recruiting clinicians give out the physically indistinguishable treatment package in allocated randomization order to the sequential participants on enrollment day (day 0). Subsequently the treatment pack number becomes the participants’ identification number.

### Intervention and control groups

On day 0, the enrolled participants will be blindly and randomly assigned to one of three 10-day treatments (minimum of 80 women per treatment arm): (1) placebo (emollient cream); (2) H_3_BO_3_ (600 mg H_3_BO_3_ compounded in emollient cream); (3) metronidazole (10 %, for a total of 37.5 mg metronidazole) intravaginal cream (Sanofi-Aventis Canada Inc. Product DIN 01926861) packaged by the study pharmacist. There is no detectable difference between the treatments in either appearance or scent.

### Study procedure and data collection

On day 0, a pregnancy test will be conducted and history will be collected by the clinician. During a pelvic examination, the clinician will ensure intact mucous membranes and anatomy, observe whether there is homogenous milky or creamy discharge (one of the four Amsel criteria), take swabs for chlamydia and gonorrhea, BV (for the Nugent score), candidiasis, and trichomonas, and perform a Whiff test using a provided standardized 10 % potassium hydroxide solution (one of the four Amsel criteria). Vaginal discharge will also be tested for pH (one of the four Amsel criteria). Where facilities permit; clue cells will be examined, as the fourth Amsel criterion. On this day, the recruiting clinician will confirm participation, eligibility, and exclusion criteria using provided protocol forms and will collect the signed consent form and the demographic and medical history questionnaires provided.

The blinded treatment pack (containing either H_3_BO_3_ compounded in emollient cream, metronidazole cream, or emollient cream) is allocated by the recruiting clinician in the randomization order to sequential participants on day 0. The participant package also contains: (1) vaginal applicator; (2) pads; (3) non-lubricated non-latex condoms; (4) a diary to record daily use of the treatment (5) information sheet outlining follow-up instructions and emergency contact numbers for the study members. Participants will self-administer the blinded treatment cream intravaginally each evening immediately prior to sleep for 10 days. The participants will be instructed to use a provided pad during day and night. Each participant will record daily compliance, side effects, and symptoms in the journal provided.

On both follow-up visits: days 17–19 (one week after the treatment end) and 40–42 (one month after the treatment end), the participant will return to the clinic that enrolled her for reassessment, a pregnancy test, and a follow-up examination, including a pelvic examination and repeat swab analysis. It will be noted whether her BV symptoms are still present, and if she had any side effects or problems during treatment. The participant will also return her daily treatment diary on the day 17 visit.

### Safety assessments

Emergency telephone contact with the investigators will be available for any questions or problems related to the treatment. On day 5 of the treatment, the participant will receive a call, text, or email from one of the investigators to determine and record compliance, side effects, BV symptoms, and satisfaction with treatment. The study pharmacist will be informed by the recruiting clinician of the participant’s full name, date of birth, and personal health number, and the study number assigned, so that the study pharmacist can enter the medication name into the British Columbia PharmaNet Database (the provincial pharmacy database). This safety measure ensures that subsequent treating physicians throughout the province will have access to details of the treatment received, in case of a safety concern and a need to unblind the participant’s medication should the participant present with an emergency. Non-emergency access to the provincial pharmacy database is not allowed, to protect the participant’s identification of the blinded treatment.

If at any time the participant reports intolerable side effects (vaginal discomfort, intolerable vaginal discharge, urticaria, or secondary yeast infection) during treatment, or exacerbation of symptoms at any point, she may voluntarily discontinue the treatment and leave the study without prejudice, and her doctor or another physician may provide treatment as per usual standard of care.

As neither metronidazole nor H_3_BO_3_ treatments provided to patients are in amounts considered toxic when taken intravaginally or if accidentally ingested, should there be any occurrence of serious adverse effects (neurological, cardiac, respiratory, gastrointestinal, or anaphylactic reactions) during any of the treatments, the study will be put on hold until an investigation can be held. In the case of serious adverse effects found to be caused by the treatment, the study will be stopped, and the study unblinded and decoded by the study pharmacist. The investigators, participants, and clinicians involved in the study would be informed for the reason for stopping the study.

### Outcomes and assessment

On days 17–19 and days 40–42, if the vaginal swab is positive for BV found by both meeting three of four Amsel criteria and having a Nugent score ≥7 and the participant is symptomatic for BV, the physician will prescribes a standard medication of his choice. This is considered a treatment failure addressing our primary and secondary outcomes: effectiveness at 7 days and 30 days after treatment end.

If the participant discontinued the treatment during the 10 days because of side effects or complained of intolerable side effects (major adverse effects) from the treatment, this is considered a treatment failure referring to our secondary outcome: safety.

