**Methods/Design:**

The BASIC (Boric Acid, Alternate Solution for Intravaginal Colonization) trial is a randomized, double-blinded, multicenter study. The study will enroll a minimum of 240 women of 16–50 years of age who are symptomatic with bacterial vaginosis. Eligible participants will have Amsel and Nugent scores confirming bacterial vaginosis. Women who are pregnant or menopausal or have other active co-infections will be excluded. Consenting participants who meet exclusion and inclusion criteria will be randomly assigned to one of three treatment groups: boric acid, metronidazole, or an inert placebo. Self-administration of treatment intravaginally for 10 days will be followed by clinical assessment at 7 and 30 days (days 17 and 40, respectively) after the end of the treatment phase. Primary outcome is a non-inferiority, per-protocol comparison of the effectiveness of boric acid with that of metronidazole at day 17, as measured by the Nugent score in 16–50 year olds. Secondary outcomes include: non-inferiority, intention-to-treat comparison of effectiveness of boric acid with that of metronidazole at day 17, analysis for both per-protocol and intention-to-treat at day 40, and safety considerations, including adverse effects requiring patient discontinuation of treatment.

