### Statistical considerations

The primary outcome measure is a non-inferiority per-protocol comparison of effectiveness of H_3_BO_3_ with metronidazole at day 17, as measured by Nugent score, in 16–50-year-olds with a *z*-based confidence interval for the difference of two proportions. This was chosen as the primary outcome measure because the immediate effect of H_3_BO_3_ after a 10-day treatment compared with metronidazole was our most important question about BV treatment. A change from a baseline Nugent score ≥7 to a Nugent score <7 is considered a cure of BV. Treatment failure will be reported as a positive Nugent score ≥7 at day 17.

Secondary outcome measures include a non-inferiority intention-to-treat comparison of effectiveness of H_3_BO_3_ with metronidazole at day 17, as measured by Nugent score in 16–50-year-olds, with a *z*-based confidence interval for the difference of two proportions. We will use this comparison to confirm the robustness of our per-protocol comparison but the per-protocol analysis will be the primary determinant of the non-inferiority test. In addition, we will conduct a non-inferiority comparison of effectiveness of H_3_BO_3_ and metronidazole at day 40, as measured by Nugent score in 16–50-year-olds analyzed on both per-protocol and intention-to treat principles, with a *z*-based confidence interval for the difference of two proportions, and safety consideration including intolerable adverse effects requiring patient discontinuation of the 10-day treatment. To control for multiple testing, we will use a Bonferroni-type correction. To account for both intention-to-treat and per-protocol analyses, and two timepoint analyses, the threshold for statistical significance will be set at 0.01 (approximately 0.05 divided by 4).

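### The protocol does not settle whether a woman given standard BV medication after failing at day 17 can count as a day-40 cure of her assigned arm, and one reading favours non-inferiority

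*Protocol article*

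**What the plan says.** Two sections of the protocol article bear on the day-40 outcome.

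**Outcomes and assessment.** This covers both follow-up visits, days 17-19 and days 40-42. The trigger for treatment outside the study drug is three of four Amsel criteria together with "having a Nugent score ≥7 and the participant is symptomatic for BV". When it is met, "the physician will prescribes a standard medication of his choice". The next sentence classifies the event: "This is considered a treatment failure addressing our primary and secondary outcomes: effectiveness at 7 days and 30 days after treatment end".

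**Statistical considerations.** Cure rests on the Nugent score only: "A change from a baseline Nugent score ≥7 to a Nugent score <7 is considered a cure of BV". Failure is stated for one visit only: "Treatment failure will be reported as a positive Nugent score ≥7 at day 17". For the later visit, "we will conduct a non-inferiority comparison of effectiveness of H_3_BO_3_ and metronidazole at day 40, as measured by Nugent score", on both per-protocol and intention-to-treat principles. The abstract lists the same two analyses. Nothing here refers to BV medication taken between the visits.

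**Study procedure and data collection** has participants return at both visits for a pelvic examination and a repeat swab. No section withdraws or excludes a woman who was prescribed other medication at day 17.

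**The concern.** The same data can give two different day-40 results. Take a woman who is Nugent-positive and symptomatic at day 17, receives a standard drug, and is Nugent-negative at day 40. If the sentence in Outcomes and assessment carries her day-17 failure forward, she is a day-40 failure. If Statistical considerations is applied as written, she has gone from Nugent 7 or above to below 7 and is a day-40 cure of the arm that failed her.

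Under the second reading the day-40 comparison measures assigned treatment plus rescue. Metronidazole, the comparator, is among the recommended treatments listed in the Background, so the rescue drug may be the comparator itself. The arm with more day-17 failures has more women to rescue and gains most. In a non-inferiority comparison, a gap narrowed in this way makes it easier to pass an inferior treatment. Day 40 supplies two of the four analyses over which the significance threshold is divided, and it is the later of the two effectiveness time points.

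**Working it through.** **Inputs from the protocol**
- Margin 10 points; one-sided 0.05 and 80% power; true difference of +8 points; 63 per group; 25% dropout; target 80 per arm (Study design).
- Metronidazole cure 70-80% (Study design); midpoint 75% used.
- Threshold 0.01 across the four analyses (Statistical considerations). Its sidedness is not stated; it is taken as one-sided here.

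**Assumptions, not in the protocol**
- Boric acid truly at 65%, exactly on the margin.
- Rescue cure c = 75%, the midpoint of the same 70-80%.
- No relapse and no late spontaneous cure.
- 60 analysed per arm (80 x 0.75).
- Share r of day-17 failures rescued: unknown, so varied.

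**The plan's own figure.** With 75% v 83%, n = (1.645 + 0.842)² x (0.75 x 0.25 + 0.83 x 0.17) / (0.08 + 0.10)² = 62.7, or 63 per group. This reproduces the stated number.

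**Day-40 cure if rescued women are scored by Nugent alone**
- p40 = p17 + (1 - p17) x r x c.
- The arm difference is therefore (day-17 difference) x (1 - r x c).
- P(declare non-inferiority) = Φ[(difference + 0.10)/SE - z], with SE² = [pM(1 - pM) + pB(1 - pB)]/60, where M is metronidazole and B is boric acid.

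**Example, r = 0.5**
- Metronidazole: 0.75 + 0.25 x 0.5 x 0.75 = 0.844.
- Boric acid: 0.65 + 0.35 x 0.5 x 0.75 = 0.781.
- Difference: -0.10 x (1 - 0.375) = -0.0625. SE = 0.0710.
- (-0.0625 + 0.10)/0.0710 = 0.528. Φ(0.528 - 1.645) = 13%; Φ(0.528 - 2.326) = 3.6%.

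| Share rescued | Metronidazole v boric acid, day 40 | Difference (points) | False non-inferiority, one-sided 0.05 | One-sided 0.01 |
|---|---|---|---|---|
| 0 | 75.0% v 65.0% | -10.0 | 5% | 1% |
| 25% | 79.7% v 71.6% | -8.1 | 8% | 1.8% |
| 50% | 84.4% v 78.1% | -6.3 | 13% | 3.6% |
| 100% | 93.8% v 91.3% | -2.5 | 47% | 22% |

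Moving c over 70-80% with half rescued gives 12-14% at 0.05 and 3.3-4.0% at 0.01. With 63 per arm, the 50% and 100% rows become 13.5% and 48.2% at 0.05.

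**When boric acid is not worse.** With equal true rates of 75%, the difference stays at zero. With the plan's +8 points, the estimate shrinks to 8 x 0.625 = +5 with half rescued and 8 x 0.25 = +2 with all rescued. The estimate is then biased against boric acid, although the chance of declaring non-inferiority barely moves with half rescued (80.2% to 80.4%, 63 per arm, one-sided 0.05).

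**The case against.** The strongest reply is that the protocol already deals with this. The sentence after the prescribing rule calls these women failures for effectiveness at both 7 and 30 days, and it can be read as carrying a day-17 failure to day 40. That reading is fair. A reader might infer that the protocol definitely scores rescued women as cures; it does not. But the sentence covers both visits and can also mean that failure at each visit counts for that visit's outcome. It also uses a narrower failure definition (Amsel, Nugent and symptoms) than the statistical section (Nugent alone), and the statistical section does not repeat it. The ambiguity remains.

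Three further points stand.
- Not every day-17 failure is rescued, because Amsel criteria and symptoms are also required. The Background says half of women with BV have no symptoms, although participants here were symptomatic at entry. The 100% row is therefore an upper bound on the share rescued, not an expected case.
- The per-protocol set is not defined in the article and may be defined elsewhere, so whether rescued women stay in it is unknown. Intention-to-treat is the clearer exposure. Dropping them from the per-protocol set would not cure the problem, because known failures would leave the denominator.
- Relapse is ignored, and rescue is assumed to work as well as first treatment. Both probably overstate the rescue gain.

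A reader might also infer that the comparison with placebo is distorted. The protocol gives no time point for that test in 16-50-year-olds, so this cannot be claimed.

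**Conclusion.** The point holds as an unresolved conflict between two sections, not as a settled scoring error. If the statistical section is followed literally, the day-40 difference shrinks by the factor (1 - share rescued x rescue cure rate). At a true 10-point deficit, with a quarter to half of failures rescued, the false non-inferiority rate is roughly 1.6 to 2.6 times nominal at one-sided 0.05 (8/5 to 13/5) and 1.8 to 3.6 times at 0.01. This rests on 75% v 65% true cure, 75% rescue cure, no relapse and 60 per arm; the rescued share cannot be obtained from the protocol.

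It would be wrong to infer that the main conclusion of the trial is at risk. The day-17 per-protocol comparison is the primary determinant of non-inferiority and is measured before any day-17 rescue can act. Only the secondary day-40 analyses are affected. The correction is worth making because it is cheap and because either reading could otherwise be chosen after the results are known.

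**What to change.** Reconcile the two sections before unblinding.

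1. Add to Statistical considerations: a woman given BV medication other than study drug before the day-40 swab counts as a day-40 failure and stays in the denominator. Make the classification sentence in Outcomes and assessment say the same.
2. Record the day-17 prescription on the case report form so that the rule can be applied.
3. Report day-40 Nugent regardless of rescue as a descriptive result.

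Do not also require Nugent below 7 at day 17. That would turn an unrescued woman who clears by day 40 into a failure and change the endpoint to sustained cure, which is a different question.

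The cost is one sentence, one data item and lower reported day-40 cure rates. In the half-rescued example they fall from 84.4% v 78.1% to 75% v 65%. No change to prescribing is proposed.

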### Statistical considerations

The primary outcome measure is a non-inferiority per-protocol comparison of effectiveness of H_3_BO_3_ with metronidazole at day 17, as measured by Nugent score, in 16–50-year-olds with a *z*-based confidence interval for the difference of two proportions. This was chosen as the primary outcome measure because the immediate effect of H_3_BO_3_ after a 10-day treatment compared with metronidazole was our most important question about BV treatment. A change from a baseline Nugent score ≥7 to a Nugent score <7 is considered a cure of BV. Treatment failure will be reported as a positive Nugent score ≥7 at day 17.

Secondary outcome measures include a non-inferiority intention-to-treat comparison of effectiveness of H_3_BO_3_ with metronidazole at day 17, as measured by Nugent score in 16–50-year-olds, with a *z*-based confidence interval for the difference of two proportions. We will use this comparison to confirm the robustness of our per-protocol comparison but the per-protocol analysis will be the primary determinant of the non-inferiority test. In addition, we will conduct a non-inferiority comparison of effectiveness of H_3_BO_3_ and metronidazole at day 40, as measured by Nugent score in 16–50-year-olds analyzed on both per-protocol and intention-to treat principles, with a *z*-based confidence interval for the difference of two proportions, and safety consideration including intolerable adverse effects requiring patient discontinuation of the 10-day treatment. To control for multiple testing, we will use a Bonferroni-type correction. To account for both intention-to-treat and per-protocol analyses, and two timepoint analyses, the threshold for statistical significance will be set at 0.01 (approximately 0.05 divided by 4).

The following are tertiary outcome measures and no formal sample size calculations were made. Minor adverse effects (side effects not causing the patient to discontinue treatment) will be reported and compared between the treatment arms but will not be considered as treatment failure. We will examine the adolescent population, the 16–19 year old subgroup, for non-inferiority for effectiveness of H_3_BO_3_, as compared with metronidazole, at the end of the study. Finally, we will test for superiority of the effectiveness and safety of H_3_BO_3_ compared with placebo in both the 16–50-year-olds and in the 16–19 year old subgroup. In addition, our study is the first to be able to examine 16–19-year-olds for the effectiveness and safety of metronidazole compared with placebo.

95 % confidence intervals will be established. Missing data (participants who fail to complete follow-up for any reason) are accounted for by an anticipated 25 % lost-to-follow-up rate. Data will be blindly collected by the outcome assessors from the participating clinics and entered into an electronic database. The study pharmacist will provide the randomization code for the data to a third-party statistician and the data will be analyzed. Self-reported participant satisfaction criteria included at the end of the daily treatment diary will use a five-point rating scale to record: effectiveness in curing BV symptoms, side effects, ease of use, likelihood they would use it again for BV treatment, likelihood they would recommend it to someone else for BV treatment.

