## Methods/Design

### Study design

Institutional review board approval was granted for this study through the University of British Columbia Clinical Research Ethics Board (H07-02330). Health Canada Clinical Trial Application Notice of Authorization was obtained on 10 May 2013 (company code 31784, file number 187476). This trial is registered with ClinicalTrials.gov (NCT00799214). This study conforms to CONSORT 2010 guidelines for randomized control trials.

Based on preliminary data, the success rate for the boric acid treatment group is predicted to be approximately 77–88 % [25, 32] in treating BV. Metronidazole would be expected to be 70–80 % [11, 12, 15–18] effective in treating BV, as compared with a 30 % success rate of a placebo group [11, 12]. The Nugent score is found to be >95 % sensitive [33] for detecting BV. We chose a non-inferiority limit of 10 %, as this will allow for a clinically relevant difference between the metronidazole treatment group and the boric acid group. Also, this is approximately 25 % of the expected difference between results obtained for the metronidazole standard treatment group and the placebo group. Accounting for a non-inferiority limit (delta) of 10 %, testing for a significance level of 0.05 and power of 80 %, we require approximately 63 subjects per group. To allow for a dropout rate of 25 %, we set a target rate of 80 subjects per treatment arm. If there is a true difference in favor of the experimental treatment of 8 %, then 126 patients (total for two groups of 63) are needed, to be 80 % sure of the upper limit of a one-sided 95 % confidence interval, using a binary outcome, non-inferiority trial power calculator [34].

We felt it important to include a placebo treatment arm in this study for different reasons: (1) this is the first randomized controlled trial to use intravaginal H_3_BO_3_; thus, comparing it to placebo for safety and effectiveness would be of clinical interest (that is, perhaps it is not comparable to metronidazole in effectiveness but it is still significantly better than placebo), (2) having a placebo group in a non-inferiority trial acts as a sensitivity assay and internal validator for this type of trial [35], (3) comparing metronidazole effectiveness and safety with results obtained for a placebo group in 16–19-year-olds has not previously been done and would also be of clinical interest.

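### The primary day-17 comparison is valid but unadjusted; a pre-specified risk difference standardised over baseline Nugent score and age would cost almost nothing, though its gain is unknown and may be close to nil

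*Protocol article*

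**What the plan says.** Under Statistical considerations, the article fixes the primary analysis as a per-protocol non-inferiority comparison of boric acid "with metronidazole at day 17, as measured by Nugent score". The method is a z-type interval for the difference between two cure proportions. Cure means moving from a baseline Nugent score of 7 or more to a score below 7. The same method is named for day 17 by intention to treat and for day 40. No covariate is mentioned.

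Baseline information is available. Participants and eligibility requires a Nugent score of at least 7 and an age of 16 to 50, so both values are known for each eligible woman. Study procedure and data collection adds that on day 0 the clinician "will collect the signed consent form and the demographic and medical history questionnaires provided", besides recording discharge, the amine (Whiff) test and pH.

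On size, Study design states: "testing for a significance level of 0.05 and power of 80 %, we require approximately 63 subjects per group". The target is then set at 80 per arm to allow for 25% dropout.

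**The concern.** When a baseline measurement predicts a binary outcome, a comparison of raw proportions leaves explainable variation in the standard error, and the confidence limit sits further from the estimate than it need. Here the outcome is a cut of the same score measured on day 0. The investigators also plan separate analyses of 16–19-year-olds, so they regard age as relevant. The Randomization section describes no stratification by either variable.

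Moving to an adjusted analysis in a non-inferiority trial often raises the worry that the estimand, and so the margin, changes. It need not. Standardising a logistic model over the trial population returns a marginal risk difference, which can be set against −10 points exactly as the raw difference would be. What is at stake is a possible modest gain in precision at almost no cost. The validity of the planned result is not in question.

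**Working it through.** **Inputs from the article (Study design).**
- Margin: "Accounting for a non-inferiority limit (delta) of 10" percentage points.
- One-sided 0.05: "to be 80 % sure of the upper limit of a one-sided 95 % confidence interval".
- Assumed advantage: "If there is a true difference in favor of the experimental treatment of 8" percentage points.
- Control rate: "Metronidazole would be expected to be 70–80" per cent. The single value used is not stated; the midpoint, 75%, is assumed here.
- Boric acid rate: "predicted to be approximately 77–88" per cent; 75% + 8 points = 83% lies inside this range.

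**Step 1: reproduce the stated 63.**
- Variance sum V = 0.75 × 0.25 + 0.83 × 0.17 = 0.1875 + 0.1411 = 0.3286.
- n = V × (1.645 + 0.842)² / (0.10 + 0.08)² = 0.3286 × 6.183 / 0.0324 = 62.7, so 63 per group. This matches.
- With the same 8-point advantage, a 70% control rate gives 73 and 80% gives 51, so about 75% is the value consistent with the article.

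**Step 2: evaluable number.** 80 × 0.75 = 60, three below 63. Inflating by division gives 63 / 0.75 = 84; multiplying instead gives 63 × 1.25 = 78.75, close to the stated 80.

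**Step 3: power with and without adjustment.** Power = Φ(0.18 / √(V(1 − R²)/n) − 1.645), where R² is the share of outcome variance explained by the baseline covariates. This is an approximation that treats R² as common to both arms. The article gives no R², so the values below are assumptions.

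| R² (assumed) | Power, n = 60 per arm |
|---|---|
| 0 | 0.7845 |
| 0.02 | 0.7916 |
| 0.05 | 0.8025 |
| 0.10 | 0.8210 |
| 0.20 | 0.8587 |

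At n = 63 with no adjustment, power is 0.8016. The R² at which 60 women carry the information of 63 is 1 − 60/63 = 0.048. If the control rate is 70%, power at 60 goes from 0.730 (R² 0) to 0.769 (R² 0.10); if it is 80%, from 0.856 to 0.886.

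**Step 4: is an R² of 0.05 likely from the Nugent score?** Entry at 7 or more truncates the covariate. Taking 10 as the top of the scale (an assumption; the article gives no upper end), only four values remain. Cure was modelled as logistic in the score, with the intercept set to give 75% or 83% cure. R² was taken as the between-score variance of the cure probability divided by p(1 − p), with numerator and denominator each summed over the two arms. Three assumed score distributions were used (even; 20/40/25/15%; 10/50/25/15%).

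| Odds ratio per point (assumed) | R² | Power, n = 60 |
|---|---|---|
| 1.1 | 0.001–0.002 | about 78.5% |
| 1.25 | 0.006–0.010 | 78.7–78.8% |
| 1.5 | 0.02–0.03 | 79.2–79.6% |
| 2.0 | 0.06–0.09 | 80.7–81.6% |

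Of the odds ratios tried, only 2.0 per point passes the 0.048 break-even. Age may add something, but the article offers no basis for saying how much.

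**The case against.** The strongest reply is that nothing here is an error. The unadjusted interval is valid, pre-specified, and of the same form as the calculation that sized the trial. An adjusted supportive analysis may well sit in a full protocol or analysis plan that is not shown. This stands, and it is why the point is only an optional improvement. It does not remove the point, because the article itself fixes the primary method.

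The second reply is that the benefit rests on a number nobody has supplied. This also stands. No section says that any day-0 variable predicts cure, and truncation of the Nugent score makes a gain below one power point quite possible.

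Three stronger readings are tempting, and the document supports none of them.
- A reader might infer that the trial falls short of 63 because covariates were omitted, or that adjustment would restore 80% power. The shortfall comes from the dropout inflation: 84 enrolled per arm would leave 63 evaluable and 80.2% power with no assumption about R². It costs 1.7 power points (80.2% against 78.5%), and 80 per arm is stated as a minimum.
- A reader might infer that adjustment makes the per-protocol arms comparable. It reduces the effect of imbalance only in the covariates included, under the fitted model. Selection after randomisation remains.
- A reader might infer that adjustment secures the trial's power more generally. Much larger influences are the assumed 8-point advantage and the 0.01 threshold under Statistical considerations. With no true difference, power at 60 is about 35%, and 38% at R² 0.10. At a one-sided 0.01, it is 54.2%, and 59.4% at R² 0.10. Modest adjustment repairs neither.

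**Conclusion.** The point holds as a minor, low-cost efficiency recommendation. The primary analysis is sound as written, but it leaves unused two baseline variables that are already in hand and that can be used without altering the estimand or the margin. With 60 per arm, 75% against 83%, and one-sided 0.05, the gain over 78.5% power is about 0.7, 1.8 or 3.6 points at an assumed R² of 0.02, 0.05 or 0.10, and essentially nil at R² near 0. The arithmetic is firm. Where in that range the trial lies cannot be determined from the document, and for the Nugent score alone the lower end is plausible.

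**What to change.** Before the randomisation code is released to the statistician, specify the following for day 17:
- Fit a logistic model for cure with treatment, baseline Nugent score and age, stating the form in which each covariate enters.
- Standardise the predicted cure probabilities over the women analysed to obtain the marginal risk difference, boric acid minus metronidazole.
- Compare its lower confidence limit, from a robust or bootstrap variance, with −10 points.
- Report the planned unadjusted interval as a sensitivity analysis.

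Describe this as a precision measure whose benefit depends on prognostic strength, with no claim that it recovers lost sample size or corrects per-protocol selection. Treat the enrolment target (84 rather than 80 per arm for 63 evaluable at 25% dropout) as a separate correction.

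The cost is a few lines of analysis text and a little programming. No extra patients, visits or data are needed.
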